### Aim 2: Implementation evaluation

In addition to the Asthma Care from Home impact assessment, we will undertake a mixed-methods implementation evaluation using the evidence-based Consolidated Framework for Implementation Research to understand how and why our intervention was effective or ineffective in producing systems change [25]. We also aim to identify contextually relevant strategies for successful implementation as well as practical difficulties in the adoption, delivery, and maintenance of Asthma Care from Home to inform wider state and potentially national rollout. The evaluation will allow us to assess implementation metrics as defined by Proctor et al (Table 2) [26].

**Table 2 pone.0304711.t002:** Implementation metrics.

	Questions addressed by each implementation factor.
**Acceptability **	Do practitioners, parents and children view Asthma Care from Home as agreeable?
**Adoption **	To what extent do practitioners and parents use resources?
**Appropriateness **	Do stakeholders perceive Asthma Care from Home as relevant & useful?
**Fidelity **	Are all component parts of the intervention delivered as planned?
**Feasibility **	Are Asthma Care from Home component parts practical to deliver within the service?
**Coverage **	How many service users of those eligible are reached?
**Cost **	How much does it cost to implement Asthma Care from Home successfully?
**Sustainability **	What factors will allow Asthma Care from Home to be scaled-up further?

#### Logic model

We have created a logic model to help develop and guide the implementation evaluation mixed methods approach to data collection (S2 Fig). The model encompasses the specific contextual factors the implementation evaluation would need to consider both within (e.g., inner context representing individual factors and organisational settings) and external to the sites (e.g., area demographics, socio-economic status) [27, 28].

In addition to the contextual factors, we have attempted to represent the measurable intervention characteristics, including the number of scheduled follow-up virtual consultations, the extent of administrative support including regular meetings with the project team and the use of project resources. The practical elements of the intervention are underpinned by theoretical principles including the 7 Critical success factors for a successful transition from hospital to home framework and the behaviour change wheel [29, 30]. Finally, we have drawn connections from these underlying theories of change to the specific outcomes we hypothesise the intervention will produce.

*Outcome measures*. Table 3 provides a summary of the outcome measures for the implementation evaluation.

**Table 3 pone.0304711.t003:** Outcome measures of the implementation evaluation.

Outcome	Methods and Measures	Participants	Time
Description of local context and practice	Socio-Economic Indexes for Areas (SEIFA) data, search of grey literature, informal contact with LHDs, project data collection logs	Project team	Ongoing throughout implementation
Fidelity to the model	Case log. To determine how the intervention is being carried out in each site as compared to the intended rollout, we will draw on trial data, which will record the specific details of model delivery. This will include recording: •Number of eligible patients participating in the study •Number of SMS send to families after discharge. •Number/frequency of virtual home visits conducted. •Attendance to webinars.	LHDs representative and project team members.	Ongoing throughout implementation
Barriers and facilitators to running the Asthma Care from Home Model	To determine an individual’s knowledge and beliefs about the model of care; relative advantages of the model of care; barriers and facilitators affecting the delivery of the intervention both from an individual and organisational perspective; the appropriateness and acceptability of the intervention; and recommendations for future implementation, we will conduct semi-structured interviews and focus groups with all participant groups at various stages during the trial. Qualitative interviews and focus groups, are guided by the Consolidated Framework for Implementation Research (CFIR)	Practitioners involved in clinical care delivery, families/carers, managers and project team.	Ongoing throughout implementation
The Acceptability, Appropriateness, and Feasibility of the model	Acceptability of intervention measure [31], intervention appropriateness measure (IAM), and feasibility of intervention measure (FIM). To measure of the perceived fit, relevance, or compatibility of evidence-based practice for a context, person, or problem.	Practitioners involved in clinical care delivery.	Implementation end (included in the 12-month practitioners involved in clinical care survey)
Practitioners buy into the model	To assess to what extent practitioners “buy into” the Asthma Care from Home model of care, and how it becomes part of routine practice, we will use the NoMAD Tool based on normalisation process theory. The NoMAD tool will assess how the intervention was incorporated into standard work responsibilities	Practitioners involved in clinical care delivery.	Implementation end (included in the 12-month practitioners involved in clinical care survey)
Family experience and acceptability of the model	The theoretical framework of acceptability (TFA) to evaluate patient acceptability of the model.	Families and carers	Implementation end (included in the 12-month family survey)

#### Data collection

Data collection will consist of: 1) Routinely collected data on enrolments, diagnoses, and demographic information; 2) Surveys with parents/carers and practitioners involved in clinical completed regarding their experiences of the service; 3) Qualitative data through focus groups and interviews with parents/carers, healthcare providers and project team members.

*Surveys*. Surveys will be collected online via REDCap, a secure web application for building and managing online surveys hosted on UNSW infrastructure.

*Families/carers*. Families/ carers at the end of the study will be asked to complete an evaluation survey to collect their perspectives on the program (Table 3). The survey will include a validated tool, based on the theoretical framework of acceptability (TFA) of health interventions tool [32]. Items will be rated on a 5-point Likert scale.

*Practitioners involved in clinical care*. All practitioners involved in clinical care delivery will be asked to complete a short online survey about their experiences with the program. The survey will include two validated instruments: the short intervention acceptability, appropriateness and feasibility measure, and the NOMAD tool (Table 3) [33–35]. Items will be rated on a 5-point Likert scale from 1 (strongly agree) to 5 (strongly disagree).

*Interviews and focus groups*. Interviews with families and carers will determine their perceptions of the acceptability of the model and any potential adaptations to the model to make it more acceptable for children and their families. Practitioners involved in clinical care and managers will specifically be asked about the features of follow up support and coordination with other professionals. Interviews with project team members will provide details about the model implementation process from an implementer’s perspective.

#### Sample size

Participants of our implementation evaluation include consenting practitioners involved in clinical care, families of 5–12-year-olds with asthma, managers and project team members.

#### Surveys

*Families/carers*. The family experience surveys will be offered to all families actively participating in the Asthma Care from Home program. Information regarding the survey will be sent to all participants at the end of the impact assessment period at 12 months to ensure the anonymity of the families. We expect to collect approximately 100 surveys across the three LHD during the whole intervention period (24 months). No power calculation has been done as we will recruit as many families as possible during this timeframe and utilise all available data.

*Practitioners involved in clinical care*. All practitioners involved in clinical care delivery will be recruited to complete a short online survey after the intervention rollout. A research team member will contact them via email with the information regarding the survey with a direct link to the survey.

*Interviews and focus groups*. Purposive sampling will be used to recruit a diverse sample of service users and providers for the interview and focus groups. Data collection for the qualitative interviews and focus groups will continue until data saturation- no new themes pertaining to the research objectives are identified with subsequent interviews. However, from previous experience, we will contact at least 40 practitioners, managers and families/carers across the three sites, ensuring diversity with regard to practice and role [36].

Families/carers and practitioners who have participated in the model of care will be recruited during the survey intervention period, including an item seeking permission to contact them about the opportunity to participate in a qualitative interview or focus group. The interview can be conducted either in person, online via video or via telephone. We aim to conduct around 20 with practitioners and 20 parents/caregivers across the three LHDs.

Additionally, a research team member will contact managers directly via phone or email to invite them to participate in an interview or focus group and provide information about the objective of the discussion. We aim to recruit at least one manager per LHD.

#### Data analysis

*Surveys*. In this study, reliability, validity and confidence will be maximised through cross verification and exploration of differences between the qualitative and quantitative, exploring and accounting for differences and mapping the perspectives of different stakeholders across the study. Quantitative questionnaire data will be exported into SPSS/STATA for analysis. Descriptive statistics will be calculated for each LHD in which recruitment is performed including information about inner and outer context, the intervention use and its acceptability. Any open-ended questions will be analysed and, where possible, a coding scheme will be developed to enable descriptive analysis, and where this is not possible, open-ended questions will undergo inductive thematic analysis.

*Interviews and focus groups*. The study team will audio-record and transcribe interviews and focus groups verbatim and thematically analyse the transcripts to identify, interpret and report on the repeated patterns of meaning within the data, influenced by the CFIR constructs and drawing from Braun and Clark’s thematic analysis approach [37]. The data collected will be de-identified in preparation for data analysis and no results will contain any information that could identify participants [37]. Where appropriate, NVivo software will aid in the coding and organisation of themes. An inductive analysis of qualitative data will be conducted to ensure openness to emerging themes not readily captured by the CFIR and Proctor and colleagues’ outcome measures. The analysis will specifically focus on key behavioural issues and motivational domains as well as the challenges surrounding intervention implementation.

### Aim 3: Economic evaluation

#### Outcome measures

An economic analysis will determine the relative cost-effectiveness of the implemented model relative to current standard care and will include a cost impact analysis for the LHDs to inform potential future scale-up of the intervention. Results of the cost-effectiveness analysis will be presented as incremental cost effectiveness ratios for our new model, demonstrating the relative cost per quality adjusted life year (QALY) through the new model. Health utilisation data captured through the impact assessment will be combined with estimated costs of health services accessed pre and post enrolment for each enrolled child. Average cost per encounter (including ED presentation, hospital admission, outpatient and GP encounters) will be applied to estimate the costs of treatment for this patient cohort and examine the differences in costs between the implemented model and traditional care.

#### Data analysis

Relevant data on the number of encounters and average costs per encounter will be obtained from the Management Support and Analysis Units in the participating LHDs. To estimate broader personal costs incurred by families, we will include survey questionnaires for families to estimate the costs associated with attending health services for their child including accommodation, parking, meals, cost of employment foregone, cost of distance travelled (per kilometre average costs for an average vehicle), and lost education opportunities (number of school days missed by the child). They will also be asked to report any out-of-pocket costs they have paid to access care or medications for their child. The expected cost impact analysis will be estimated based on the down-stream resource utilisation and funding impacts of the new model, from a health service provider and funder perspective (participating LHDs and NSW health system).

Cost-effectiveness will be measured by evaluating differences in the incremental cost-effectiveness ratio of the Asthma Care from Home model compared to the situation prior (pre-implementation) to intervention using historical data. Cost effectiveness results will be expressed as a series of incremental cost-effectiveness ratios depicting the cost per incremental change in ED presentations, hospitalisation avoided, and differences in QALYs between the two groups.

## Discussion

Asthma remains the most common chronic respiratory disease in children and adolescents in Australia and continues to have a high associated burden of care [1, 2]. Our model of care offers a solution to the current fragmented and inadequate Australian healthcare system. This model aims to standardise the care provided for children with asthma and provide easy access to in-depth educational resources and support tools for families, healthcare providers and community services so a child’s asthma can be managed effectively outside of a hospital setting and closer to home.

We have used a pre-post trial design, which will allow us to determine the changes in health services used due to our model of care. The pre-intervention period of health service utilisation for each participant will be incorporated as a temporal control. A notable strength of this design is that since the same group serves as its control, it can help control for individual differences that might confound the results in studies involving separate control groups. This can enhance the internal validity of the findings. Additionally, the gathered pre-intervention period data will incorporate five years to account for the disruption of the COVID-19 pandemic, which has been well documented to have resulted in an unseasonable decrease in asthma hospitalisations during lockdown periods [38].

In analysing our data, we will use an Interrupted Time Series Analysis (ITS) methodology. ITS analysis is one of the most effective quasi-experimental evaluation methods and has been used in many health intervention evaluations [39]. It makes full use of the longitudinal nature of the data, allowing us to control for time-varying confounders such as seasonality and co-occurring competing interventions, thereby addressing critical threats to internal validity and causal inference.

An added advantage of our methodology is integrating a theory-informed mixed-method process evaluation. This inclusion allows us to comprehensively grasp the obstacles and enablers of implementing this initiative within real-world practice, and facilitates the identification of strategies conducive to its sustained implementation [40]. Concurrently, we will undertake an economic evaluation to establish a viable rationale for healthcare organisations to allocate resources towards adopting the Asthma model of care. This will substantiate the tangible advantages of such an uptake on the Australian healthcare system.

Our trial has several limitations. First, the one-group pre-post-trial design limits our ability to assess and compare the effects of our initiative with usual care. However, the rationale for selecting this design is that the intervention involves providing a standardised asthma discharge package to eligible children, rendering the inclusion of a control waitlist impractical. After consultation with our LHD partners, a randomised controlled trial was deemed unsuitable due to the standardised nature of the intervention, thus making the proposed intervention essentially a part of standard care. We will collect and use self-reported participant data, which may introduce reporting bias. However, given the mixed-method methodology that will be employed, and the diversity of outcomes evaluated, the potential for reporting bias is minimal.

In conclusion, this study aims to significantly enhance access to asthma care, particularly targeting children in underserved communities like those living in rural and remote areas. By assessing implementation and economic factors, our research will provide comprehensive understanding of the effectiveness and viability of the model to help integrate it into standard practice. By utilising local resources, we can ensure the sustainability of improved healthcare services and help shed light on the potential for scaling up this model to benefit a wider population of children facing asthma-related challenges in underserved regions.

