### Study population

Between March 2023 and June 2024, children aged between 5–12 years old presenting to ED on one or more occasions or admitted to the general paediatric ward on one or more occasion in the last 12 months with asthma at selected study hospital sites within the three LHDs will be eligible to participate in the study. For those that fulfil all eligibility criteria (Box 1), each participant will be followed for a period of 12 months after enrolment. Informed written consent was sought from parents/carers of eligible children electronically via REDcap software.

Box 1Inclusion criteriaChildren aged between 5–12 years old.1 or more ED presentations or 1 or more hospital admission in the last 12 monthsChildren with current or history of physician-diagnosed asthmaChildren attended EDs or admitted to general paediatric wards with asthma exacerbation or asthma-related illnesses (e.g. wheeze) at hospitals within the three participating LHDs during the study periodParents/carers of non-English speaking background but understand English and do not require interpreter.Exclusion criteriaChildren with complex conditions e.g., genetic disorders, complex cardiac diseases etc.Children with high-risk and complex asthma who are already known to tertiary paediatric respiratory specialists.Children with significant developmental delays or comorbidities that will significantly limit their ability to participate in the study.Both parents/carers who do not understand English and require interpreterFamilies who do not have permanent housing e.g., live in a shelter.

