### Aim 1: Impact assessment

#### Data collection

Changes in health service use for participating children will be evaluated by comparing the period of up to 5 years prior to their enrolment into the program (pre-intervention) and the period of up to 12 months following enrolment (post-intervention). This information will be gathered primarily from electronic care records at baseline (retrospectively gathering data on health service use in previous 5 years) and 12 months post-enrolment. Five years data pre-enrolment will be used to account for disruption from the COVID-19 pandemic.

As we are following up participants through time in each site, the pre- intervention time period of health service use for each participating site will serve as its own control for the post-intervention time period of health service use, that is, temporal control.

*Outcomes measures*. All outcome measures for the impact assessment will be assessed at baseline, 6 months, and 12 months post-intervention (Table 1). We will measure the changes over time (i.e., pre-intervention at baseline and post-intervention at 6-month and 12-month), and differences between intervention and temporal control groups on all indicators.

**Table 1 pone.0304711.t001:** Outcome measures of the impact assessment.

Outcome	Measure(s)	Source	Time point

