#### Data analysis

Interrupted time series (ITS) analysis will be used to assess the change in the time series patterns (intercept and slope) of health service use before and after intervention.

ACT score, asthma related quality of life, medication adherence, parent and child quality of life and family reported experiences will be compared at enrolment, 6 and 12 months after enrolment into the service. We will describe the outcomes at each time point using mean, standard deviation, median, and inter-quartile range. Since each participant will have three repeated measures over time, we will use multi-level regression analysis to examine the effect of the intervention on these outcomes, including in the models, a fixed effect for the intervention status (0 = pre-intervention, 1 = 6-month post-intervention, 2 = 12-month post-intervention) and calendar time of enrolment into the intervention for each participant, as well as a random effect of the Local Health District (LHD) to explore the degree of variation in the intervention effect by LHD. Our final model will exclude the random term in the presence of a statistically non-significant random effect. We will also consider participants are clustered within each LHD and use generalised estimating equations (GEE) approach in the regression analysis to account for the clustering.

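### The Discussion says the interrupted time series controls for co-occurring competing interventions, but a one-group before/after series cannot remove a change in care that arises at or after enrolment

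*Protocol article*

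**What the plan says.** All places are in the protocol article.

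- **Discussion, paragraph on ITS:** the method is credited with this property: "allowing us to control for time-varying confounders such as seasonality and co-occurring competing interventions, thereby addressing critical threats to internal validity and causal inference".
- **Discussion, paragraph on design:** the pre-post design is one "which will allow us to determine the changes in health services used due to our model of care".
- **Aim 1, Data collection:** the contrast is described as "comparing the period of up to 5 years prior to their enrolment into the program (pre-intervention) and the period of up to 12 months following"; both windows are counted from each child's entry. The earlier period of each site "will serve as its own control for the post-intervention time period of health service use, that is, temporal control".
- **Aim 1, Data analysis:** the ITS is to "assess the change in the time series patterns (intercept and slope) of health service use before and after intervention". No comparison site, control outcome, co-intervention term or calendar-time term is named for health service use. Calendar time of enrolment is named only for the questionnaire outcomes.
- **Study population:** enrolment is staggered by child: "Between March 2023 and June 2024, children aged between 5–12 years old presenting to ED".
- **Discussion, limitations:** "the one-group pre-post-trial design limits our ability to assess and compare the effects of our initiative with usual care". Concurrent changes in care are not mentioned, and the earlier statement about competing interventions is not withdrawn.

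**The concern.** A segmented regression on a single exposed series projects the earlier trend forward and calls the departure from it the effect. That is sound as far as the earlier trend would have continued. If another service, policy or access change moves asthma presentations in the same months, the departure contains both influences and the before/after contrast cannot divide them. The Discussion therefore claims a property that the described design does not have.

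The claim carries weight. It supports the statement that changes due to the model of care can be determined, it bears on the research question about state-wide scale-up, and the economic evaluation also compares with the historical period. An unrelated fall in presentations would be read as benefit, and an unrelated rise would hide a real benefit.

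**Working it through.** The plan states no figure for this point, so there is none to reproduce. The check has three steps. The size and timing of the background change and the baseline rate are assumptions, because the documents give none.

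**Inputs from the protocol article.** 270 children analysed (Sample size calculation); up to 5 years before, taken as 60 months, and up to 12 months after (Aim 1, Data collection); change in intercept and slope (Aim 1, Data analysis); enrolment March 2023 to June 2024, which is 16 calendar months (Study population).

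**Step 1: what the model absorbs.** The model fitted to noise-free monthly means is

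log μ(t) = a + b·t + c·post + d·post·(t − 60) + annual sine and cosine terms.

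The true programme rate ratio (RR) is 1. The underlying series has a log-linear trend of −0.003 per month and a seasonal amplitude of 0.3 on the log scale.

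| Background change | Apparent programme effect |
|---|---|
| None (trend and season only) | RR 1.00 |
| Step to 0.90, 0.80 or 0.70 at programme start | level change 0.90, 0.80 or 0.70 |
| Step to 0.80 six months after start | mean post-period RR about 0.90 |
| Step to 0.80 twelve months before start | mean post-period RR about 0.94 |

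Trend and season are removed. A step at the start passes through in full, and a step at another time passes through in part.

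**Step 2: staggered enrolment.** The same model was fitted in time relative to enrolment, with enrolment spread evenly over 16 months. A background step to 0.80 in calendar month 1, 5, 9 or 13 of the enrolment window gives a mean post-period RR of 0.89, 0.86, 0.86 or 0.88. With no background step it is 1.00. Staggering dilutes the bias and does not remove it. When one term per calendar month was added, the programme RR returned to 1.00 (noise-free, step in month 5). That model is not stated for health service use.

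**Step 3: false-positive rate.** Assume 1.0 presentation per child-year, so 270 × 1.0 / 12 = 22.5 expected per month. Counts are Poisson, the step falls at programme start and there is no programme effect. The standard error (SE) of the level change comes from the inverse Poisson information matrix of the Step 1 model, here with a flat underlying series. Rejection for the level change is Φ(−1.96 − log RR/SE) + 1 − Φ(1.96 − log RR/SE). The joint test of level and slope uses a chi-square with 2 degrees of freedom and noncentrality λ.

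| Unrelated fall | log RR | SE | Level change significant | λ | Joint test significant |
|---|---|---|---|---|---|
| 10% | −0.105 | 0.139 | 12% | 1.37 | 17% |
| 15% | −0.163 | 0.142 | 21% | 3.15 | 34% |
| 20% | −0.223 | 0.145 | 34% | 5.76 | 57% |

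The nominal rate is 5%. At 0.7 presentations per child-year the level-change figures are about 10%, 16% and 25%, and at 1.5 they are about 15%, 29% and 47%. The table takes the least favourable timing, a step exactly at programme start; staggered enrolment would lower it.

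**The case against.** Much can be said for the plan, and part of it stands.

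- **The limitation is disclosed in general terms.** The one-group design is the first limitation listed, with reasons why a waitlist control and a randomised trial were not used. This is fair, but the text speaks of comparison with usual care, not of concurrent changes, and it leaves the claim about competing interventions in place.
- **Not every background change is credited to the programme.** A reader might infer that any change in care passes one for one into the estimate. The documents do not support that: earlier smooth trends are absorbed by the slope, and full pass-through needs a step that coincides with the start of exposure.
- **Unexposed time exists in the same calendar months.** A child enrolled in June 2024 contributes pre-enrolment time that overlaps the follow-up of a child enrolled in March 2023. Calendar terms could exploit this, and an analysis plan that is not shown may contain them. But that time comes from children selected for having a later event, and none of it remains once enrolment closes.
- **No actual co-intervention is identified.** A reader might take the Background on pandemic-era changes in practice, or the use of a statewide education body, as evidence of one. The pandemic changes fall largely in the five-year pre-period, which was chosen with that disruption in mind. Nothing says that the statewide body changed its activity during the study.
- **A simple 12-versus-12-month rate comparison would look worse.** At 1.0 per child-year it rejects in about 22%, 44% and 69% of trials for falls of 10%, 15% and 20%. It is not the planned analysis, so those figures should not be used here.

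**Conclusion.** The claim is wrong as written. The described ITS, in one exposed group with a temporal control, does not control for co-occurring competing interventions. A departure from the prior trend that another change in care causes at or after enrolment is credited wholly or partly to the programme. Under the stated assumptions, an unrelated 20% fall would appear as a mean post-period rate ratio of about 0.86 to 0.89 with staggered enrolment. A fall of 10% to 20% exactly at programme start would raise the false-positive rate from 5% to about 12–34% (level change) or 17–57% (joint test) at 1.0 presentation per child-year.

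These figures illustrate sensitivity and do not predict bias in this trial, since the documents report no background change in the study period. Nor does the point show that the design is unusable. It shows that the stated causal strength must be reduced.

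**What to change.** **Needed (wording only, no cost).**
1. In the Discussion paragraph on ITS, delete the reference to co-occurring competing interventions from the list of what the method controls.
2. In the paragraph on design, replace the attribution of changes to the model of care with a statement that the estimate is the programme effect plus any concurrent change in care that departs from the earlier trend.
3. Name this in the limitations paragraph.

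**Low-cost supporting analyses from the same records.**
- Add calendar-time terms to the health-service ITS and use the staggered enrolment. The cost is some precision, and the unexposed time of later enrollees is selected on their having an event.
- Report non-asthma ED attendances of enrolled children as a negative-control outcome. This can reveal a general change in ED use or access, though not a change confined to asthma care.

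**Optional, as a sensitivity analysis only.** A concurrent aggregate series of non-enrolled children or non-participating districts. It is not selected on a recent presentation as the enrolled children are, and non-enrolled children at the same hospitals may receive parts of the programme. A difference between the series could therefore mix selection and spill-over into the estimate.
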